#### Analysis

Data analysis is performed according to the intention to treat principle.

Short term outcome measures are compared by calculating relative risks and their 95% confidence intervals. Future fertility is assessed by life table analysis. Kaplan-Meier curves are constructed, estimating the cumulative probability of time to spontaneous IUP and repeat EP. If a spontaneous viable IUP does not occur, follow up ends at the last date of consultation, or at the start of in vitro fertilisation (IVF) treatment or the date of tubal surgery. Spontaneous conceptions that occur after failed IVF treatment will be registered. The log-rank test is used to test differences between the Kaplan-Meier curves for statistical significance. The differences between both treatment modalities are expressed as a fecundity rate ratio with 95% confidence interval, calculated through Cox proportional hazard analysis.

Changes in health related quality of life over time, and differences between the two groups will be measured using analysis of variance.

Depending on differences of equivalence between the strategies, the economic evaluation will be a cost-effectiveness analysis or a cost-minimisation analysis.

Patient's preferences are analysed by differences in outcome of the DCE.

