### Inclusion criteria

Hemodynamically stable patients ≥ 18 years of age, with either a visible EP on TVS (an ectopic ring or an ectopic mass and/or fluid in the pouch of Douglas) together with plateauing serum hCG concentrations < 1,500 IU/L, and those women with a PUL in combination with plateauing serum hCG concentrations < 2,000 IU/L, are eligible for the trial. The difference in serum hCG cut-off levels for these two entities is based on our previous studies [5,7]. Patients with a viable EP, signs of tubal rupture, active intra abdominal bleeding or a contra indication for MTX (e.g. abnormalities in liver or renal function or at full blood count) are not included.

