### Randomisation

Randomisation is performed by a web-based randomisation program, using a computer program with stratification for hospital and serum hCG concentration (< 1,000 IU/l versus 1,000–2,000 IU/l).

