### Outcome measures

#### Primary outcome measure

The primary outcome measure is an uneventful decline of serum hCG to an undetectable level (< 2 IU/l) by the initial intervention strategy, i.e. expectant management or a single dose systemic MTX.

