#### Power calculation

Assuming an uneventful decline of serum hCG of 60% in the expectant management group and of 90% in the MTX group, and assuming a power of 80% and a significance level of 5%, 36 patients in each group are needed [6,15,22-24].

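### Randomisation is stratified by initial hCG, but the named analyses do not use that stratum; stratifying the relative risk would gain a little precision at almost no cost

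*Protocol article*

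**What the plan says.** The Randomisation section allocates by a web-based program, "using a computer program with stratification for hospital and serum hCG concentration", with hCG split at 1,000 IU/L.

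The Primary outcome measure section defines a binary endpoint: "The primary outcome measure is an uneventful decline of serum hCG to an undetectable level (< 2 IU/l) by the initial intervention strategy".

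The Analysis section covers that endpoint with one sentence: "Short term outcome measures are compared by calculating relative risks and their 95% confidence intervals". For fertility it names Kaplan-Meier curves, the log-rank test and a Cox model. It attaches neither the hCG stratum nor hospital to any of these, and it does not say that the relative risk is crude.

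The Power calculation section works from overall rates only, "Assuming an uneventful decline of serum hCG of 60% in the expectant management group and of 90% in the MTX group", with 80% power and a 5% significance level, and concludes that "36 patients in each group are needed".

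**The concern.** Stratified allocation balances the arms on hCG, so differences in success between hCG strata largely drop out of the comparison between arms. A crude standard error still counts those differences as noise. If success depends on initial hCG, the crude interval is then a little wider than it need be and its test a little conservative. Analysing by the stratum used to randomise removes that surplus. With 72 women, modest precision is worth having when it is free. Naming the estimator in advance also closes off a later choice between crude and adjusted results.

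**Working it through.** **Inputs from the protocol article.** Success 60% (expectant) and 90% (MTX), 80% power, 5% significance, 36 per group; two hCG strata. Sidedness is not stated; two-sided is taken.

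**Assumed, because the documents do not give it.** The gap in success between low and high hCG: 0 to 40 points in the expectant arm and half of that in the MTX arm, with the overall rates held at 60% and 90%. The share of women in the low stratum: 50% or 75%.

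**Step 1: the plan's own figure.** The exact power of an unstratified two-sided Fisher test is 78.5% at n = 35 and 80.04% at n = 36 per group. So 36 is reproduced. (The normal approximation gives 32 without and 38 with continuity correction.) The inputs are overall rates only, so no gain from stratification is built in.

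**Step 2: crude against stratified standard error.** Let M and E be the successes in the MTX and expectant arms, m_i and e_i the successes in stratum i, n_i the women per arm in that stratum, and n = 36.

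- With equal n_i in both arms, the Mantel-Haenszel relative risk is Σ(m_i/2) / Σ(e_i/2) = M/E, the same as the crude estimate. Only the standard error changes.
- Crude variance of log RR: 1/M + 1/E − 2/n.
- Mantel-Haenszel variance: 1/M + 1/E − 2·Σ(m_i·e_i/n_i)/(M·E).

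At expected counts, M = 32.4 and E = 21.6, so the crude variance is 0.03086 + 0.04630 − 0.05556 = 0.02160.

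*20-point gap, equal strata* (expectant 70%/50%, MTX 95%/85%, n_i = 18): m = 17.1 and 15.3, e = 12.6 and 9.0. The sum is 11.97 + 7.65 = 19.62. The variance is 0.07716 − 2 × 19.62/699.84 = 0.02109. The ratio of standard errors is √(0.02109/0.02160) = 0.988.

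*40-point gap, equal strata* (80%/40%, 100%/80%): m = 18 and 14.4, e = 14.4 and 7.2. The sum is 14.40 + 5.76 = 20.16. The variance is 0.07716 − 2 × 20.16/699.84 = 0.01955. The ratio is 0.951.

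**Step 3: simulation.** 40,000 trials per scenario, 36 per arm, exact balance within hCG strata. Ranges are over the two stratum shares.

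| Gap (expectant arm) | SE ratio, stratified/crude | Power, crude | Power, stratified |
|---|---|---|---|
| 0 | 1.000 | 86.2% | about 86.0% |
| 10 points | 0.997–0.998 | 86.2% | 86.0–86.1% |
| 20 points | 0.988–0.991 | 86.5% | 86.7–87.0% |
| 30 points | 0.972–0.979 | 86.8–87.2% | 87.7–88.5% |
| 40 points | 0.950–0.962 | 87.3–87.9% | 89.3–90.7% |

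Coverage of the crude 95% interval runs from 94.9% to 96.6%. Power here exceeds 80% because the log-RR interval is less conservative than Fisher's test.

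**Step 4: hospital as a second stratifier.** Blocks within hospital-by-hCG cells would often be left incomplete, so hCG balance would be only partial. With such blocks (block size and number of hospitals assumed), the direction is unchanged. The power gain runs from about 0.5 point at a 20-point gap to about 4 points near 40, and the stratified test stays within its 5% size.

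**The case against.** The strongest objection is that the crude analysis is read from silence. A Mantel-Haenszel relative risk is also a relative risk, and a condensed article may leave the strata to a fuller document that is not shown. This stands as a limit: no sentence is wrong, and the documents do not prove that the analysis will be crude. But the Analysis section lists its methods one by one without the stratum, and the sample size draws on no strata. Naming the stratified estimator is therefore a concrete improvement.

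Three stronger readings are tempting and are not supported.

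- *Power is lost.* A reader might infer a shortfall. The 36 per group reaches 80.04% without any stratification, so only an extra gain is forgone.
- *The interval is 10 to 20% too wide.* Such figures need very strong prognosis and no treatment effect. With 60% of women in the low stratum and success of 90% v 52.5% in both arms, within-stratum variance is 0.6 × 0.09 + 0.4 × 0.2494 = 0.1538 against a total of 0.1875. The crude standard error is then 1/√0.82 = 1.10 times the stratified one. With 95% v 45% the factor is 1.21. These gaps of 37.5 and 50 points have no source in the documents, and the figures assume exact balance.
- *The protocol shows hCG, or diagnosis, to be prognostic in this trial.* It gives no reason for stratifying. Of the separate ceilings for visible EP and PUL it says only "The difference in serum hCG cut-off levels for these two entities is based on our previous studies", which concerns eligibility. Chance imbalance in diagnosis does not bias a randomised comparison, and crossing diagnosis with hCG would thin the cells.

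**Conclusion.** The point holds as a minor improvement in precision. The trial randomises by hCG stratum and the analyses named do not use it. If hCG is prognostic, the crude interval is slightly conservative. The planned power is met either way, and no false-positive rate is raised.

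At 60% v 90%, stratifying is worth close to nothing for a gap of 0 to 10 points. It gives about 1 to 2% off the standard error and under 1 point of power at 20 points, and about 4 to 5% and 2 to 4 points near 40. These sizes rest wholly on the assumed gap, the assumed smaller gap in the MTX arm and the assumed stratum shares. The direction rests only on hCG being related to success.

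**What to change.** In the Analysis section, state that the primary relative risk is the Mantel-Haenszel estimate stratified by the hCG stratum used at randomisation, with its 95% confidence interval, and that the crude relative risk is shown alongside. Stratify the log-rank test and the Cox model by the same factor.

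Leave hospital out of the primary estimate and say why: with 72 women its cells would be sparse. Use visible EP v PUL in a sensitivity analysis at most.

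The cost is a sentence or two; the stratum is already recorded at randomisation. The downside is negligible: if hCG is not prognostic there is no gain, and in the simulation power moved by about 0.2 points at most.

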In these non-surgical treatments, the pregnancy is not removed and as a consequence there is a remaining risk of tubal rupture. Therefore, intensive serum hCG monitoring is mandatory to detect impending treatment failure and/or inadequately declining serum hCG concentrations [13,14]. The risk of tubal rupture combined with the need for meticulous follow-up is likely to cause distress in the patient because of uncertainty about treatment outcome [15]. Non-surgical treatment modalities may therefore have a negative impact on the patients' health related quality of life.

In some women presenting with suspected EP, the pregnancy cannot be identified on TVS [16,17]. These women with a so called pregnancy of unknown location (PUL) can be managed expectantly with monitoring of serum hCG to identify whether a PUL turns out to be an intra uterine pregnancy (IUP), an EP, a failing PUL with an uneventful serum hCG decline to undetectable levels, or a persisting PUL with plateauing serum hCG concentrations [18].

Women with a visible EP but with low and plateauing serum hCG concentrations and women with a persisting PUL have thus far been offered medical treatment with MTX [17,19]. However, there is no evidence on the effectiveness of MTX as compared to expectant management. This study compares both treatment options in these particular subgroups of women, representing about 10% of women with suspected EP.

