## Objective

To study whether expectant management is an alternative to treatment with systemic MTX in a single dose im regimen in women with an EP and low but plateauing serum hCG concentrations in terms of tubal rupture, future pregnancy, health related quality of life and costs.

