#### Secondary outcome measures

Secondary outcome measures are (re)interventions (additional MTX injections or surgical procedures for persistent trophoblast and/or clinical signs), treatment complications, health related quality of life, financial costs, and future fertility. Moreover, patients' preferences will also be assessed.

Health related quality of life is assessed by standard self administered psychometric questionnaires with established viability and reliability at different time points, i.e. before randomisation, after one week, four weeks and three months.

Costs are expressed in direct costs with data on costs and used resources in the participating centres.

Future fertility is defined as time to the occurrence of a spontaneous viable IUP. A viable IUP is defined as the presence of fetal cardiac activity at a gestational age of ≥ 12 weeks. If an IUP does not occur, follow-up ends at the last consultation. In addition to IUP, repeat EP is also assessed. The date of occurrence of an EP will be determined from the first day of the last menstrual period.

Patients' preferences are assessed by an online questionnaire using a discrete choice experiment (DCE) based on characteristics of both interventions and will be compared with a control group, recruited among women visiting the infertility clinics of the participating hospitals.

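### The relative risk is the only stated comparison for rare short-term harms in 36 women per arm, and it gives no upper limit on the excess harm of expectant management when the MTX arm has no events

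*Protocol article*

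**What the plan says.** In the protocol article, the Analysis section gives one rule for this group of outcomes: "Short term outcome measures are compared by calculating relative risks and their 95% confidence intervals". It states no absolute measure beside the ratio.

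Secondary outcome measures places the harms under that rule. Its list includes "re)interventions (additional MTX injections or surgical procedures for persistent trophoblast and/or clinical signs), treatment complications". Tubal rupture is not named there. It is, however, the first item in the Objective, which judges expectant management "in terms of tubal rupture, future pregnancy, health related quality of life and costs". The Background explains why: with non-surgical treatment "the pregnancy is not removed and as a consequence there is a remaining risk of tubal rupture".

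The Power calculation rests on the primary outcome only: "Assuming an uneventful decline of serum hCG of 60% in the expectant management group and of 90% in the MTX group", from which "36 patients in each group are needed". No section gives an expected rate of rupture, complications or surgery.

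**The concern.** A ratio suits an outcome that is common in both arms, as the primary outcome is. It suits a rare harm in a small trial poorly, because one or both arms may have no events. With none in either arm the ratio is 0/0. With none in the MTX arm its denominator is zero.

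The trial asks whether women can safely be left untreated at first. If few or no ruptures or operations occur, the useful quantity is the largest risk, or excess risk, still compatible with the data. In those two situations a relative risk cannot supply it, and a report of no events could be taken to mean more than 36 women per arm can show.

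**Working it through.** **Inputs.** 36 per group, 60% v 90%, 80% power and 5% significance (Power calculation); relative risk with 95% interval (Analysis). The harm rates are assumptions, because the documents give none: 1%, 2%, 3% and 5% per arm.

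**The plan's own figure.** Enumerating a two-sided Fisher exact test at 60% v 90% gives power of 78.5% with 35 per group and 80.0% with 36. The stated 36 per group is reproduced.

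**Primary outcome.** At the planned 10% failure under MTX, the chance of no failures in that arm is 0.9^36 = 2.3%. The relative risk works here.

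**How often arms are empty.** For risk p in both arms, the chance that a given arm has no events is q = (1-p)^36. Both are empty with probability q², and only the MTX arm with probability q(1-q).

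| Assumed p | q (MTX arm empty) | q² (both empty) | q(1-q) (only MTX empty) |
|---|---|---|---|
| 1% | 69.6% | 48.5% | 21% |
| 2% | 48.3% | 23.3% | 25% |
| 3% | 33.4% | 11.2% | 22% |
| 5% | 15.8% | 2.5% | 13% |

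With unequal assumed risks of 5% expectant and 1% MTX, both arms are empty in 0.158 × 0.696 = 11.0% of trials, and only the MTX arm in 0.696 × (1 - 0.158) = 58.6%.

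**What the relative risk (expectant over MTX) gives in each case.**

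- 0 v 0: undefined, with no bound. Adding 0.5 to each cell gives 1.0 (0.02 to 49), which is uninformative.
- Events only under expectant management: the ratio is infinite and the log-scale interval fails. A score (Koopman) interval has a lower limit, 0.27 at 1 v 0 and 0.54 at 2 v 0, but no upper limit.
- Events only under MTX: the estimate is 0. The log-scale interval fails, but the score interval has an upper limit, 3.76 at 0 v 1 and 1.85 at 0 v 2.

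**What absolute measures give.**

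- Exact (Clopper-Pearson) upper limit for 0/36: 1 - 0.025^(1/36) = 9.7%.
- Newcombe interval for the difference at 0 v 0: the Wilson upper limit for each arm is 1.96²/(36 + 1.96²) = 3.84/39.84 = 9.6%, so the interval is -9.6 to +9.6 points.
- The same method gives +2.8 points (-7.1 to +14.2) at 1 v 0, +5.6 (-4.9 to +18.1) at 2 v 0, and +8.3 (-2.7 to +21.8) at 3 v 0.

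A difference and two finite limits are available in every case.

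**The case against.** The strongest reply is that this is one sentence in a journal article. Interval method and zero-cell handling commonly belong in a full protocol or analysis plan that is not shown, so their absence is no finding. That is right as far as it goes. The point survives because the article itself chose the measure, and no later choice of interval method gives a relative risk a useful bound at 0 v 0, or an upper limit when only the MTX arm is empty.

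A reader might infer that the rule yields neither estimate nor bound whenever one arm has no events. The documents do not support this. It would require the log-scale interval, which the article does not specify. With one empty arm a score interval keeps one finite limit, and if the empty arm is the expectant one, that limit bounds the relative harm. The chance of at least one empty arm (90.8%, 73.3%, 55.6% and 29.1% at the four assumed risks) therefore overstates the problem.

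Other parts of the reply also stand:

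- Rupture is not a listed outcome, and its place under the rule is inferred from the Objective and from complications and surgery. The Abstract names treatment success where the Objective names rupture.
- Surgery need not be as rare as rupture, because Short term follow up also links it to a need for more than four MTX injections.
- A relative risk does not rule out reporting counts, from which a reader could work out the 9.7%.
- An interval of -9.6 to +9.6 points does not settle safety. The underlying limit is the sample size, and the Discussion foresees a meta-analysis with a parallel trial.

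These lower the severity, but they do not make the ratio a suitable sole measure for rare harms.

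**Conclusion.** The point holds, as a minor one. The relative risk is the only stated comparison for short-term harms. At 36 per arm it is undefined and sets no bound in 48.5%, 23.3%, 11.2% and 2.5% of trials at assumed risks of 1%, 2%, 3% and 5% in both arms. In a further 21%, 25%, 22% and 13% only the MTX arm is empty, and the excess harm under expectant management has no upper limit. These percentages rest on assumed rates, equal risks and independent events. At 10% in both arms the both-empty case falls to 0.1%.

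The primary outcome is not affected. Nor do the documents support a demand that any safety statement rest on the upper limit for rupture or surgery: the plan makes no such rule and does not need one for this point.

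**What to change.** In Analysis, keep the relative risk with its 95% interval for the primary outcome. For treatment complications and for surgery, add the number and percentage per arm with an exact (Clopper-Pearson) 95% interval, and the between-arm risk difference with a score-type (Newcombe) 95% interval. State that tubal rupture is counted among the complications.

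This costs about one sentence, uses data already collected and changes no clinical rule. The only drawback is that a result with no events will carry a visibly wide interval. Per-arm counts would also let a 0 v 0 result contribute to the foreseen meta-analysis on the risk-difference scale, whereas standard pooling of relative risks would drop it.

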### Follow up

#### Short term follow up

In both groups weekly serum hCG measurements will be performed until serum hCG is no longer detectable. Serum hCG concentrations are expressed in IU/L (conversion factor to SI unit, 1.00 according to the World Health Organization Third International Standard 75/537). Seven days after a MTX injection liver and renal function and full blood count are checked. Complications will be registered in the Case Record Form.

In patients treated expectantly, treatment with systemic MTX (single shot 1 mg/kg im) is started whenever at any of the weekly follow up visits the serum hCG concentration has risen > 15% of the prior value. Expectant management is continued if the serum hCG concentration falls by > 15% of the prior value [20]. In case of a persistent plateauing serum hCG concentration, defined as < 15% fall or < 15% rise, the serum hCG concentration is assessed after 48 hours to ensure it is not increasing. If it is increasing as described above, treatment with systemic MTX as described above is installed. Whenever hemodynamic instability and/or clinical signs of tubal rupture (i.e., increasing abdominal pain in combination with falling haemoglobin level and signs of intra abdominal haemorrhage on TVS) occur, surgical intervention is carried out.

In patients treated with MTX, an additional MTX injection is given in case the serum hCG concentration on day 7 has declined <15% of the initial value on day 1 (start of treatment) [11]. If the serum hCG concentration fails to fall by at least 15% during any successive week of follow-up, repeated doses of MTX are given, with a maximum of three additional injections [21]. In case of hemodynamic instability and/or signs of tubal rupture, i.e., increasing abdominal pain in combination with falling haemoglobin level and signs of intra abdominal haemorrhage on TVS, or whenever more than four MTX injections are required, surgical treatment is indicated.

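### Fertility follow-up has two different end rules, and one of them stops at an undefined tubal surgery that can itself result from the allocated treatment

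*Protocol article*

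**What the plan says.** The endpoint is set in the protocol article under Secondary outcome measures: "Future fertility is defined as time to the occurrence of a spontaneous viable IUP". The same section gives the end of observation: "If an IUP does not occur, follow-up ends at the last consultation". No other stopping event is named there.

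The Analysis section gives a longer list for the same endpoint. Without a spontaneous viable intrauterine pregnancy (IUP), follow-up ends at the last consultation, "or at the start of in vitro fertilisation (IVF) treatment or the date of tubal surgery". It adds: "Spontaneous conceptions that occur after failed IVF treatment will be registered". No role in the analysis is given to those conceptions. The same section declares: "Data analysis is performed according to the intention to treat principle". It plans Kaplan-Meier curves, a log-rank test and a Cox fecundity rate ratio.

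Surgery appears elsewhere as part of the allocated strategies. Under Short term follow up, haemodynamic instability or "clinical signs of tubal rupture" leads to surgery in expectantly managed women, and the same triggers apply in the methotrexate (MTX) arm. In that arm there is one further trigger: "whenever more than four MTX injections are required, surgical treatment is indicated". Secondary outcome measures counts surgical procedures among the reinterventions.

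**The concern.** Two sections prescribe different datasets for one endpoint. An analyst who follows the outcome definition keeps an operated woman under observation; one who follows the Analysis section stops her clock on the day of the operation.

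The second rule has a further problem. Nothing in it exempts surgery for the index pregnancy, so it covers an event that happens after randomisation and can be caused by the strategy under test. Kaplan-Meier, log-rank and Cox methods all assume that censored women have the same later hazard of conception as those who stay under observation. For a woman operated on for rupture or failed treatment, this is doubtful.

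The Objective asks whether expectant management is an alternative to MTX, and names both tubal rupture and future pregnancy. A route by which one strategy could impair fertility runs through rupture and surgery to fewer conceptions. Censoring at surgery takes that route out of the fertility comparison, and the error then leans towards finding the strategies alike.

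**Working it through.** **The plan's own figure.** The article gives no expected rate of conception, IVF or surgery. Its one design figure, 36 per group, concerns the primary outcome (60% v 90%, power 80%, 5%; two-sided assumed, since this is not stated). Exact enumeration of Fisher's test at 36 per group gives power 80.0%, so the figure is reproduced. Nothing below changes it.

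**The two rules side by side.**

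| Event without prior IUP | Secondary outcome measures | Analysis |
|---|---|---|
| Last consultation | ends follow-up | ends follow-up |
| IVF start | not named | ends follow-up |
| Tubal surgery | not named | ends follow-up |

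**Illustration of censoring at surgery.** Every input except the 24-month horizon (Long term follow up) is an assumption:
- a constant monthly hazard of spontaneous IUP giving 50% at 24 months: h = ln(2)/24 = 0.02888, the same in both arms before surgery;
- a share s of women operated on at 0.5 month;
- a hazard after surgery of r × h.

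With censoring at surgery, the curve reflects only the hazard h, so it estimates 1 − exp(−24h) = 50.0% in each arm, whatever s and r are. The log-rank test and the Cox ratio use the same censored times and also show no difference.

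With operated women followed to 24 months:

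F(s, r) = (1 − s) × 0.500 + s × [1 − exp(−0.5h − 23.5rh)]

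The bracket equals 0.0143 for r = 0, 0.2980 for r = 0.5 and 0.5000 for r = 1. For surgery in 20% v 5%:

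- r = 0: 0.8 × 0.5 + 0.2 × 0.0143 = 0.4029; 0.95 × 0.5 + 0.05 × 0.0143 = 0.4757; difference 7.3 points.
- r = 0.5: 0.8 × 0.5 + 0.2 × 0.2980 = 0.4596; 0.95 × 0.5 + 0.05 × 0.2980 = 0.4899; difference 3.0 points.
- r = 1: 0.500 in both; difference 0.

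If 10% are operated on in each arm and r = 0, both arms stand at 45.1%. The level is overstated by 4.9 points, but the difference between arms is not distorted. The sign follows the surgery rates: with 5% v 10% and r = 0 the values are 47.57% v 45.14%, a hidden difference of 2.4 points in favour of the arm with less surgery.

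**IVF start.** Let g = −ln(1 − p)/24 be the hazard of starting IVF. If nobody conceives spontaneously afterwards, the observed 24-month probability is h/(h + g) × [1 − exp(−24(h + g))]. For p = 10%, 20% and 30% this is 47.7%, 45.4% and 42.9%, against 50.0% from the censored curve. The two agree if the hazard is unchanged after IVF start.

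**Precision.** Treating the outcome as a simple proportion with 36 per group, the 95% half-width for 46.0% v 49.0% is 1.96 × √(0.460 × 0.540/36 + 0.490 × 0.510/36) = 0.23, or about 23 points. For 40.3% v 47.6% it is also about 23 points.

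**The case against.** The strongest reply is that tubal surgery may not mean the rescue operation at all. The term occurs only in the fertility rule, next to IVF, while the rescue is described elsewhere in general terms as surgery. It could mean a later operation that, like IVF, changes the chance of spontaneous conception. This is a fair reading, but the wording does not limit the term to it. An undefined term that decides whether a treatment consequence is censored needs a definition under either reading.

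It can also be said that intention to treat fixes the arm in which a woman is analysed, and the Analysis section does not depart from that. This is correct as far as it goes: no woman is moved or excluded. What fits badly is the purpose, since a comparison of strategies as allocated is meant to include their consequences.

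The 20% v 5% has no source in the article. The design gives expectantly managed women with rising hCG MTX before any surgery, so operations may be few or similar in both arms. At 36 per group, a shift of 3 to 7 points is also small beside a half-width of about 23 points. Both points stand, and they limit how far the trial's own conclusion could change.

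A reader might also infer more than the text supports:
- That the harmed women are removed. They remain at risk until the operation; only if it falls in the first weeks is nearly all their fertility time lost.
- That IUP and repeat ectopic pregnancy are censored at each other. The Analysis section says "Kaplan-Meier curves are constructed, estimating the cumulative probability of time to spontaneous IUP and repeat EP", but its list of stopping events includes neither. A woman can have a repeat ectopic pregnancy and a later IUP.
- That both cumulative probabilities are necessarily too high. This needs a lower hazard after the censoring event, or a reading of the curve as a real-world probability.
- That censoring at IVF start is an error. Given an endpoint restricted to spontaneous conception, it answers a recognised question about fecundity in the absence of IVF. The article only leaves that question unstated.

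**Conclusion.** The point holds for the conflict between the two sections and for censoring at an undefined tubal surgery. As worded, the Analysis rule permits informative censoring at a consequence of the allocated strategy, on an outcome that the Objective names.

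The size cannot be computed from the article. Under the stated assumptions, with surgery in 20% v 5%, a true difference of 3.0 points (hazard halved after surgery) to 7.3 points (no spontaneous conception after surgery) would show as none. The bias is zero if fecundability is unchanged after surgery, and the difference between arms is undistorted in this model if surgery is equally frequent. For IVF start the issue is an unstated estimand. This is a secondary outcome, so the matter should be corrected but does not threaten the primary analysis or the 36 per group.

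**What to change.** 1. State one end-of-follow-up rule and use it in both Secondary outcome measures and Analysis.
2. Define tubal surgery, saying whether it covers operations for the index pregnancy, later operations or both.
3. In the main fertility analysis, do not censor at tubal surgery. Keep operated women in their allocated arm to 24 months. Report the surgery-censored analysis as a sensitivity analysis.
4. For IVF start, either state that the estimand is spontaneous conception in the absence of IVF, or add a cumulative-incidence analysis with IVF start as a competing event. In either case, say how the registered conceptions after failed IVF are used.

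The cost is mainly wording. Six-monthly questionnaires to 24 months are already planned for both arms and ask about infertility treatment, pregnancies and their outcomes. The plan must make clear that they continue after surgery, because the present Analysis rule could be read as ending contact there. The downside is slightly lower cumulative probabilities if surgery does reduce conception, and less comparability with any earlier reports that censored at surgery; the sensitivity analysis covers the second.
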